#### 2.4.2. Secondary Outcomes

This pilot study will be used to robustly examine the suitability and appropriateness of the secondary outcome measures (e.g., tinnitus severity, hearing function, depression, anxiety, cognitive function, and quality of life) and make necessary changes in preparation for a full trial. Descriptive statistics and confidence intervals will be reported. The small sample size may hinder a statistically significant outcome. Furthermore, changes in neuronal activity will be assessed by comparing electrophysiological measurements during sham stimulation and DBS.

Tinnitus severity will be assessed with the Tinnitus Functional Index (TFI) [62]. The TFI is a validated self-report questionnaire that measures the overall severity of tinnitus and provides coverage of multiple tinnitus severity domains. This questionnaire is the most appropriate responsive measure of treatment-related change. The TFI is translated and validated for Dutch native speakers [63].Tinnitus loudness and burden will be measured by VAS. This will be performed three times daily within a week, which is repeated four times during the study. Furthermore, these VAS scores will be used to assess the effect of stimulation on tinnitus during surgery. VAS ratings for tinnitus loudness and burden are often used in both clinical practice and experimental and descriptive research as a measure of subjective symptoms [64]. Both scales have been shown to correlate with the scores on Tinnitus Questionnaires [65].The hearing function will be assessed with pure tone and speech audiometry. These are clinical standard audiometric tests. Furthermore, subjective hearing will be evaluated using patient feedback.Cognitive functioning will be measured using a validated test battery for standard DBS care. These include the Boston Naming Test, Verbal Fluency, Letter Fluency, 15 Words Test, Trail Making Test part A and B, and the Stroop Color-Word Test.Quality of life and psychological functioning will be assessed by the following psychological questionnaires: 36-Item Short Form Health Survey (SF-36), Beck Depression Inventory II (BDI-II), Beck Anxiety Inventory (BAI), and Hospital Anxiety and Depression Scale (HADS).Neurophysiological measurements: electrophysiological data and auditory brainstem responses will be recorded before and after surgery (T0 and recovery) and at the end of treatment periods I and II (T1 and T2). Furthermore, local field potentials (LFP) will be recorded during surgery and before the implantation of the pulse generator. Details are described under ‘Neurophysiological assessments’.

Dependent on the results of the primary and secondary outcomes, future implementation procedures might be adapted or in case of adverse events, terminated. These adaptations depend not only on the feedback of the individual participants but also on expert judgment. For example, in case the patients describe the questionnaire procedures to be too burdensome, it could be considered to shorten these. Another example, based on expert judgment, could be rethinking the two times six weeks crossover design in case no short-term effects are reported. 

## 3. Intervention

### 3.1. Implantation of DBS Electrodes and Internal Pulse Generator

A two-staged surgery will be performed. First, bilateral DBS electrodes will be implanted. Tinnitus is a complex disorder for which to date the underlying mechanisms are not entirely clear. The auditory system is organized bilaterally, with a large number of interconnections and information crossing partially (80%) after the cochlear nucleus. To investigate the safety and feasibility bilateral implantation was opted for. Following a standard stereotactic surgical procedure, DBS electrodes will be inserted in the MGB of the thalamus and monitored by radiological and electrophysiological measures. The placement will be conducted under local anesthesia. A CT cerebrum will be carried out and fused with a pre-operative MRI in order to plan the exact trajectory. First, a micro-electrode (InoMed, Emmendingen, Germany) will be inserted. Neurophysiological recordings will be performed in 0.5 to 1 mm steps from 10 mm above and maximally 5 mm below the target with a multi-channel system (InoMed, Emmendingen, Germany) [66]. Simultaneously, at each step, a sequence of auditory stimuli will be presented, which is designed based on known signal processing characteristics of the thalamus [67] and to maximize the likelihood of evoking a reliable response. The amplitude of these responses relative to the spontaneous activity will be used to confirm electrode placement. After the identification of the ventral and dorsal border of the MGB, test stimulation will be applied using 130 Hz, a pulse width of 120 µs and a voltage starting from 0.5 V up to 5 V, or until undesired side effects occur. Stimulation is monopolar, the deepest contact of the electrode is the anode and the battery is the cathode. Stimulation amplitude will be adjusted stepwise. The patient will be asked repeatedly to rate the loudness and burden of the tinnitus sound using VAS. Furthermore, the neurologist will test for undesired side effects. The stimulation electrode will be placed once an optimal effect and acceptable or absent side effects are reached. After placement and fixation of both stimulation electrodes (Medtronic, model 3389) the stereotactic frame will be removed and electrodes will be externalized to enable the recording of LFPs postoperatively. 

After surgery, the patient will be transferred to a neurosurgical medium care unit. On the second post-operative day a CT cerebrum will be made to confirm the definite electrode positioning. After one or two days the pulse generator (Medtronic, Activa PC model 37601) will be subcutaneously placed under general anesthesia and the electrodes will be connected. One or two days postoperative, the patient can be discharged. After the end of the trial, follow-up as standard DBS care will be provided. 

### 3.2. Stimulation Parameters

Based on the results in rats it is expected that only high-frequency stimulation will be effective for tinnitus reduction [43]. The following stimulation parameters will be used as the minimum and maximum values during the optimization period to determine optimal stimulation parameters: stimulation frequency (2–200 Hz), pulse width (60–450 μs), and voltage (starting from 0 to a maximum of 5 V). Initially, the stimulation will be bilateral with the same parameters on both sides. Voltages will be increased symmetrically depending on the clinical effect and side effects. In case of stimulation induced side effects, bilateral stimulation can be adapted to unilateral stimulation. During treatment, patients will visit the outpatient clinic weekly. During this period, side effects and tolerability of the stimulation in daily life are evaluated; however, no instant change in tinnitus is expected due to the complexity of the disorder and the anticipated burden and duration of tinnitus. Following the treatment episode, there will be a one-week period for washout of a possible residual therapeutic effect. 

### 3.3. Neurophysiological Assessments

EEG will be recorded with surface electrodes applied to the scalp in accordance with the 10–20 international system standard. Just before the implantation of the pulse generator, cables are externalized, which enables simultaneous recordings of LFPs from the depth electrodes in the MGB. 

For each session, several recordings with and without auditory stimulation will be obtained. In the first phase, resting-state activity will be recorded with eyes open and eyes closed. These initial recordings serve to establish baselines for task-independent neural oscillatory activity, network activity, and coherence (assessed on the basis of dominant spontaneous low-frequency oscillations and their variability). In the second phase, auditory brainstem responses will be recorded using a standard protocol to probe auditory brainstem function before and after surgery. In the third phase, activity will be recorded during experimental auditory stimulation. The respective measures will allow assessing of basic characteristics of auditory function in general, and sensory gating in particular (i.e., adaptive filtering based on predictable feature-based and temporal information) in accordance with the adopted model. These measures have been previously obtained via surface EEG recordings in humans [68,69] and preliminary data show comparable responses recorded from the thalamus in the animal model.

Taken together, these measures allow for assessing fundamental signal coding (linear vs. event-related), time-course (temporal relation of thalamic and surface responses), and functional (deviance processing, regularity, predictability, gating) aspects of auditory function. Dysfunctional processing would correspondingly be indexed by desynchronization, lack of suppression effects, temporal decoupling (reduced correlation between thalamic and surface responses), and overall high variability. 

### 3.4. Randomization and Blinding

Randomization will be performed directly after the period of stimulation optimization by an independent institution, the Clinical Trial Center Maastricht (CTCM). Patients will be randomly assigned to one of the two study groups. The investigator who adjusts DBS parameters cannot be blinded. All other investigators and the patient are blinded to the study group. In case the patients are considered unblinded due to the nature of the stimulation the protocol will be carried out as planned. Only in the case of medical concerns, the patient and investigators will be unblinded in order to provide the care needed.

### 3.5. Data Collection and Management

Data handling will be organized according to the “FAIR guiding principles for scientific data management and stewardship” [70]. This will be carried out in cooperation with the CTCM, which is a local center that facilitates human research. Data will be collected by data entry in Castor electronic data capture (EDC); a cloud-based, password-protected data management system providing a backup on a secured server. Audit trailing provides basic data to backtrack a file to its origin. Paper versions of questionnaires will be kept in a locked closet in the research office. All data will be anonymously coded. The key will be available to the project leader only. Data collection is monitored by the CTCM; a specific monitor is appointed to the study who will follow up on the progress and adherence to the protocol. The monitor will perform periodic checks. A data safety monitoring board, comprising a statistician and two neurologists, is instituted which periodically reviews and evaluates the accumulated study data concerning participant safety, study conduct, progress, and efficacy. The data safety monitoring board receives and reviews the progress and acquired data of this trial and provides the research team with advice on the conduct of the trial.

### 3.6. Statistical Analyses

The safety and feasibility outcomes will be reported descriptively. Descriptive statistics with 95% confidence intervals will be used to present preliminary data of secondary outcomes such as tinnitus (severity, loudness and distress), anxiety, depression, hearing function, quality of life, and cognitive functioning. These data will provide some insight into population characteristics and might indicate potential changes in mean scores between the intervention and sham stimulation.

### 3.7. Sample Size

As this is a pilot study, no formal sample size calculation was performed. Only a small sample size will be used because a large burden is being placed on the participants. Additionally, there is uncertainty about potential benefits and the fact that the effects of surgery are still unknown, even though it is expected to be safe. Based on previous first-in-human DBS studies [24,58,71], we expect to adequately address the safety and the proof of concept purpose of the study by including six patients. In these invasive first-in-human trial small sample sizes are not uncommon. Furthermore, this number of patients will enable the collection of preliminary results that will provide meaningful information about the differences between the intervention and sham stimulation. In case of the withdrawal of a patient or in case of incomplete data there will be no replacement of individual participants.

### 3.8. Patient and Public Involvement

Patients from the Dutch tinnitus support group were involved in the development of this protocol. During information meetings, aspects of the study were discussed such as feasibility and eligibility criteria. Furthermore, patients were involved in the development of patient information. 

## 4. Discussion

One of the main ethical considerations in this study is balancing risks and benefits. The potential benefit of the intervention is a reduction of tinnitus loudness and tinnitus burden. Risks of this minimally invasive and reversible form of functional neurosurgery are surgery-related complications (e.g., cerebral hemorrhage or infarction, CSF leak, seizures, meningitis or encephalitis), hardware failure (e.g., lead rupture, extension fibrosis, device migration) and stimulation related side effects. These latter effects are unknown as clinical MGB DBS has not been performed before. The function of the MGB is primarily hearing thus other side effects than hearing-related effects are less likely. Animal studies did not show hearing loss, anxiety or locomotion-related side effects in DBS in subcortical auditory structures [43,47,48]. We also reviewed possible side effects based on the brain structures surrounding the MGB. The MGB is located posterior to the subthalamic nucleus. The MGB is 8mm wide, 6mm long and 6.5mm high with its largest volume at -3.5mm from the AC-PC (anterior commissure-posterior commissure) plane. Considering the relatively large size of the MGB, current spread outside the MGB is unlikely if the DBS electrode is positioned in the center. Neighboring structures of the MGB are structures similar to other commonly used stimulation targets. The current spread to the anterior side of the MGB could result in internal capsule effects. These side effects are known from subthalamic nucleus (STN) DBS treatment for dystonia and Parkinson’s disease. The possible side effects of internal capsule stimulation are dysarthria, muscle contractions, and gaze paresis. Posterior to the MGB the ventricle can be found. Possible side effects are known from anterior nucleus of the thalamus (ANT) DBS which has also a border at the ventricle. Antero-medially the sensory thalamus is located which is targeted when performing DBS to treat pain. More medially the fields of Forel are located. Possible side effects are known from STN DBS in which current spread also may occur to the fields of Forel which can result in disturbances of speech, postural stability and gait. Laterally to the MGB the optic tract is located. We know from globus pallidus internus (GPi) DBS that stimulation of the optic tract elicits phosphenes. All these side effects from current spread to surrounding regions are elicited by stimulation and thus reversible. Taking this together, MGB DBS could induce changes in auditory sensation, and there is a slight risk for side effects due to current spread. In case of undesired side effects, stimulation parameters can be adapted or stimulation can be turned off. The principal investigator will immediately inform the data safety monitoring board and the medical ethical committee in case of serious side effect. 

In relation to correctly and carefully evaluating risks and benefits, patient recruitment and extensive informed consent are crucial steps. The primary inclusion criterion is that patients need to be refractory to current treatment (e.g., cognitive behavioral therapy); second, sufficient hearing is required and patients cannot be candidates for cochlear implants. In a refractory patient population, patient selection is an important factor. Patients should have gone through all available proven treatments without significant success. This treatment could be the last resort for these patients when all else has failed. However, this could also affect their decision-making, making them eager to participate in the hopes of a cure. Therefore, patients should be informed about the implications and the uncertainties concerning the outcome extensively during the informed consent procedure. Thus, creating realistic outcome expectations and emphasizing the potential effects or the potential absence thereof. To evaluate whether a patient will be able to cope with a potential negative outcome (no result or side effects) a multidisciplinary team is involved in this study. Additionally, both the potential health benefits as well as the scientific gain need to outweigh the possible risks. In order to maximize the scientific benefit one should try to gather as much information as possible to expand the fundamental knowledge. The potential health benefit should be aimed at increasing the participant’s quality of life. For this reason, a balance needs to be struck to obtain the most beneficial situation for both science and the participant [72]. 

A questionnaire study showed that about 20% of general tinnitus patients are willing to undergo DBS surgery in case of a 50% chance of successful treatment. The willingness increased with the number of therapies already tried [73]. Further, patients would be willing to pay 20 times their monthly income to be treated. Most patients would accept a risk of mild side effects, and almost half of the patients would accept a risk of severe side effects [73]. A caveat in patient selection is that desperate patients might see this experimental treatment as a last resort and rush through the informed consent [74]. These circumstances make this group of patients vulnerable and inclusion should carefully be contemplated when informed consent is discussed. Included patients will receive a heavy burden by undergoing a surgical treatment that could be perceived as a last remedy. This could potentially lead to a bias based on effort justification. We aim to minimize the bias by using a combined crossover and randomized double-blind design. The crossover ensures that every patient receives each treatment in a different order, counterbalancing the treatment phases. The double-blind randomization ensures that neither the participant nor the researcher can influence the outcome as they are unaware of the condition. The rationale of the study is for the majority based on animal studies. The assessment of tinnitus in rats (GPIAS) and the method for DBS is at least not fully translatable to humans. An additional limitation is that generalizability to the target group of severely affected tinnitus patients might be challenging due to the heterogeneous nature of tinnitus and the small sample size of this pilot feasibility trial. Still, by carefully evaluating safety and feasibility in this pilot study, we will be able to determine how MGB DBS is received by participants, and optimize a follow-up study in terms of patient support, patient inclusion, surgical procedure and choice of stimulation parameters.

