#### 2.4.1. Primary Outcomes

The primary focus of this pilot study is to assess safety and feasibility. Safety will be assessed by reporting the rate and grade of all surgical and stimulation induced adverse events in the study sample during the study period. Feasibility will be assessed in terms of the acceptability of the intervention, by taking qualitative interviews at all major time points (T0, T1, T2, T3; see Table 3), and by comparing satisfaction during sham stimulation and DBS. 

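### Safety terms do not agree: hardware and unattributed events are named neither in the primary safety outcome nor in the one immediate-report trigger the article states

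*Protocol article*

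**What the plan says.** The article touches on safety events in three places.

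- **Discussion, first paragraph (risks listed).** Surgical risks are called complications, with haemorrhage, infarction, CSF leak, seizures and brain infection as examples. The list continues with "hardware failure (e.g., lead rupture, extension fibrosis, device migration) and stimulation related side effects". Of the stimulation effects it says "These latter effects are unknown as clinical MGB DBS has not been performed before".
- **Discussion, end of the same paragraph (immediate reporting).** "In case of undesired side effects, stimulation parameters can be adapted or stimulation can be turned off". The next sentence is the reporting commitment: "The principal investigator will immediately inform the data safety monitoring board and the medical ethical committee in case of serious side effect".
- **Section 2.4.1 (primary safety outcome).** Safety is assessed by "reporting the rate and grade of all surgical and stimulation induced adverse events in the study sample during the study period".

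Section 3.5 adds routine oversight: a data safety monitoring board that "periodically reviews and evaluates the accumulated study data concerning participant safety, study conduct, progress, and efficacy".

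**The concern.** Safety is a primary focus of this pilot, and the article says the target has not been stimulated in humans before. The list of risks, the definition of the safety outcome and the trigger for immediate reporting should then cover the same events. They do not. The Discussion lists hardware failure as a risk, but neither the outcome nor the trigger names it. Events that cannot be assigned to a cause are also named in neither.

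Both definitions also depend on attribution if taken literally. An event enters the primary safety outcome if it is judged surgical or stimulation-induced, and it meets the trigger if it counts as a side effect, which in that paragraph mostly means an effect of stimulation. That judgement is hard to make where the effects of stimulation are not yet known. What is at stake is complete safety capture: an event judged unrelated, or attributed to the device, has no stated place in the primary outcome, and the reported rate would reflect the attribution as well as what happened to the patients.

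**Working it through.** The document gives no figure to reproduce here, so the check sets the passages side by side.

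**Step 1: what the trigger term means where it is used.** The Discussion's risk paragraph gives surgery, hardware and stimulation three different nouns, and only the stimulation class is called side effects. The paragraph then goes through neighbouring structures and describes the side effects of current spread, stating that they are elicited by stimulation and reversible. The sentence just before the reporting commitment treats side effects as something handled by changing the stimulation settings or switching it off, which does not describe a haemorrhage, a meningitis or a broken lead. Sections 3.1 and 3.2 also use the term for effects of stimulation.

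**Step 2: whether the usage is uniform.** It is not. The second Discussion paragraph counts side effects as part of a negative outcome in general, and the third uses the term for the risks of DBS when reporting a questionnaire study on willingness to undergo the surgery. The narrow meaning is the natural one in the risk paragraph but is not forced by the article as a whole.

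**Step 3: coverage by class of event.**

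| Class of event | Listed as a risk (Discussion) | Named in primary safety outcome (2.4.1) | Named by immediate-report trigger, read literally (Discussion) | Within periodic board review (3.5) |
|---|---|---|---|---|
| Surgical | yes | yes | no | yes |
| Hardware | yes | no | no | yes |
| Stimulation | yes | yes | yes, if serious | yes |
| Other or unattributed | not listed | no | no | yes |

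Two of the four classes (hardware, and other or unattributed) are named in neither definition. Surgical events are in the outcome but outside the literal trigger. Only stimulation events are in both.

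**Step 4: whether attribution can carry this weight.** The Discussion calls the stimulation effects unknown, and Section 3.7 says the same of the effects of surgery. Under Section 3.4 everyone except the investigator who adjusts the settings is blinded to group. The article does not say who attributes events. If a blinded investigator does, that person must judge whether stimulation caused an event without knowing whether stimulation was on; if the unblinded one does, the judgement is made with that knowledge. A definition that does not depend on cause avoids the choice.

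**Step 5: whether another sentence closes the gap.** No other sentence in the article states a trigger for immediate reporting. Section 3.5 covers all the classes, but periodically.

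**The case against.** The strongest reply is that this is loose drafting in a condensed article. The reporting sentence closes a narrative paragraph in the Discussion and is not part of an operational safety section. Definitions of serious events and expedited-reporting rules are commonly left to the full protocol, which is not shown, and Section 2.2 places the study under the national human-research act and records ethics approval. The trigger carries no qualifier, whereas the article adds one elsewhere when it wants the narrow sense, so it may mean any serious untoward event. Hardware events might likewise be counted as surgical in Section 2.4.1. Other safeguards are stated: periodic board review, weekly visits during treatment (Section 3.2), withdrawal for urgent medical reasons (Section 2.3) and unblinding for medical concerns (Section 3.4).

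Much of this stands, and it rules out three stronger readings that a reader might infer:

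- **That serious surgical or hardware events are excluded from immediate reporting.** The sentence states one trigger and does not say that it is the sole one. Nor does the article describe a formal attribution step before reporting.
- **That the trial has no broader expedited rule.** The article cannot show this.
- **That delayed escalation would expose further patients.** This would need a board interval and an implantation schedule, and the article gives neither.

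What the reply does not remove is the mismatch among terms the article does state. The outcome definition in Section 2.4.1 is in the Methods and is qualified by cause. The reporting sentence, wherever it sits, is a commitment, and the article itself distinguishes immediate from periodic information to the board.

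**Conclusion.** The point holds as an inconsistency among stated definitions. The article lists three risk classes, defines its primary safety outcome by two of them, and states an immediate-report trigger whose term, in its own paragraph, mostly matches one. Hardware and unattributed events are named in neither definition.

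The size is modest. No estimate, sample size or test depends on it. Periodic board review still covers all accumulated safety data, so none of these events is outside oversight. The conclusion rests on a literal reading of Section 2.4.1 and on taking the trigger term as its own paragraph mostly uses it; it carries no claim about what the full protocol contains. It still deserves correction, because safety is a primary outcome and attribution is least reliable when the effects of the target are unknown.

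**What to change.** 1. **Section 2.4.1.** Define the primary safety outcome as the rate and grade of all adverse events during the study period, regardless of cause. Record attribution as a separate field with the categories surgery, device, stimulation, and other or unknown. Summaries by cause can still be given from that field.
2. **Discussion, reporting sentence.** Reconcile the trigger with Section 2.4.1 and with the risk list in the same paragraph, so that it refers to serious adverse events across all the listed classes, whatever the attribution. If the full protocol already contains such a rule, a reference to it is enough.

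The cost is a few sentences of text, slightly more recording, and a few more expedited reports in a six-patient study. Some recorded events will be unrelated to the intervention; the attribution field lets the reader see which. Design, sample size and treatment schedule do not change.
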